##### Outcomes

#### Primary clinical outcome

Live birth rate based on the number of live births after 24 weeks gestation within the 10.5-month post-egg collection follow-up period.

#### Secondary outcomes

Acceptability and pain rating of the ES procedure, a Visual Pain Scale (Likert) to assess their pain and tolerability assessment of the procedure within 30 min of the initial ES procedure, 1 day later and then again 7 days after the ES.Implantation rate based on a positive serum beta human chorionic gonadotropin (hCG) on approximately day 14 following the egg collection or by a positive urine pregnancy test.Clinical pregnancy rate: an observation of viable intrauterine pregnancy with a positive heart pulsation seen on ultrasound at/after 8 weeks gestation.Miscarriage rate as measured by spontaneous pregnancy loss (including pregnancy of unknown location prior to 24 weeks gestation within the 10.5-month post-egg collection follow-up period.Ectopic pregnancy as measured by the rate of pregnancy outside the normal uterine cavity.Multiple birth rate defined as the birth of more than one living fetus after completed 24 weeks gestation.Preterm delivery rate as measured by live birth after 24 weeks but before 37 weeks gestation within the 10.5-month postegg collection follow-up period.Stillbirth rate based on the delivery of a stillborn fetus showing no signs of life after 24 weeks gestation within the 10.5-month post-egg collection follow-up period.Details of participant’s IVF cycles including number of eggs retrieved, number of embryos generated 1 day after egg collection, quality of the embryos transferred (using National External Quality Assessment Service (NEQAS) grading) and the number of embryos replaced and day of embryo replacement.AEs.Health resource use of the participant and patient costs.

The trial includes a health economic component to assess the cost of the intervention per extra live birth from an NHS and social care perspective. Resource use will include the intervention costs for ES, the cost of IVF treatment, visits to the Assisted Conception Unit and for those who conceive antenatal and postnatal visits, delivery costs and any hospital stays not related to birth for both mother and baby. The resource use questionnaire will collect information on contacts with midwife and general practitioner visits. A Patient Cost questionnaire will collect time taken to travel to appointments and loss of productivity. Unit costs will be derived from appropriate national sources and will include; NHS reference costs, Personal Social Service Research Unit costs and the Office of National Statistics.^18–20^ The resource use questionnaire will be designed for this study and will draw on data collection tools developed in The School of Health and Related Research and those collated by the Database of Instruments for Resource Use Measurement.

##### Blinding

Since this trial evaluates objectively measured outcomes (pregnancy rates) that are unlikely to be affected by a placebo effect, participants will not be blinded to treatment allocation; it is therefore not necessary to perform a sham procedure for the control group. The study statistician, TSC and health economist will be blinded to the allocation.

### Trial monitoring and oversight committees

The trial will be overseen by the TSC and the DMEC, membership of both will consist of independent experts in the field. The TSC will include a patient representative. Both committees will review recruitment, study progress and AEs. The DMEC will receive monthly reports of recruitment and AEs and, at their meetings, will also consider emerging evidence from other trials or research on ES. They may advise the chair of the TSC at any time if, in their view, the trial should be stopped for ethical reasons, including concerns about patient safety.

Day-to-day running of the trial will be coordinated by the TMG, consisting of the grant coapplicants, plus members of the Jessop Wing Fertility Unit, Sheffield CTRU and Patient representatives.

### Statistical analysis

Primary analysis will be performed on the intention-to-treat population (all participants randomised into the trial). All statistical exploratory tests will be two tailed at 5% nominal level. Baseline demographic (eg, age), physical measurements (eg, BMI) and health-related data will be described and summarised overall and for both treatment groups. The women, not the IVF cycle, will be the unit of analysis. If the woman fails to get pregnant or does not have IVF treatment, they will be included in the analysis of the primary outcome as a negative outcome (ie, non-live birth). For sensitivity analyses, PP analyses will also be undertaken which will be defined as for ES participants in the intervention group, receiving the ES procedure as documented in the study protocol and undergoing IVF/ICSI in the subsequent menstrual cycle, including embryo transfer. For the control group, the PP population will receive IVF/ICSI including embryo transfer. Subgroup analyses will be undertaken to explore the effect of important variables related to the participant and their treatment on the primary and secondary outcomes. These subgroups are:Day of embryo transfer (day 2, 3, 4, 5 or 6).Fertilisation method (IVF, IVF or ICSI, ICSI (spilt)).Type of protocol (long or antagonistic).Embryo transfer (single or double) and whether the embryo was fresh or frozen.Previous history of consecutive miscarriages (0–2 vs ≥3).

AEs will be reported as a proportion of all women randomised. AEs including SAEs will be compared between the two groups using a Fisher’s exact test, χ^2^ test or negative binomial regression model in case of repeated events per woman (as appropriate). A 95% CI for the difference in AE rate between the groups will also be calculated with associated point estimate depending on the method used.

Health economic results will be presented in the net-benefit framework and will allow for uncertainty using bootstrapping and probabilistic sensitivity analysis.

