## Background

The use of local endometrial trauma known as endometrial scratch (ES) to improve implantation rates in women undergoing assisted conception was first described in 2003.^1^ The procedure has since been explored in several studies mainly focusing on women with recurrent implantation failure and has been shown to significantly increase pregnancy rates by almost double.^2–4^ However, uncertainty remains as to the therapeutic effect of ES, due to heterogeneity of the populations included—and the timing and exact protocol of ES used—in previous evaluations.^5 6^ Three systematic reviews have summarised the evidence, however, each included different studies.^2 7 8^ A recent Cochrane review included 14 randomised studies: 7 in women with previous cycle failure, 5 in an unselected population and 1 in a first-time cycle.^8^ The live birth rate (LBR) meta-analysis combined trials regardless of the population (ie, number of previous in vitro fertilisation (IVF) cycles) and included five studies, reporting a risk ratio (RR) of 1.42 (95% CI 1.08 to 1.85), p=0.02. The odds of achieving a clinical pregnancy were also increased following ES with an RR of 1.34 (95% CI 1.11 to 1.62), p=0.002. The one trial conducted in women undergoing their first IVF cycle indicated the procedure was harmful with an OR of clinical pregnancy rate of 0.30 (95% CI 0.14 to 0.63), p=0.002.^9^ Notably, this trial performed the ES procedure at the time of oocyte retrieval and not in the month prior to the IVF cycle. Despite the concerns around the quality of evidence in using ES and that many of the trials undertaken so far have been small (most <150 participants), ES has been widely adopted into routine clinical practice in women with recurrent unsuccessful implantation and is currently being provided in some fertility units where women are having IVF/intracytoplasmic sperm injection (ICSI) for the first time.^10 11^ Two large trials are currently in progress to determine if ES is beneficial in women undergoing their second IVF cycle^12^ and a sample of women undergoing any IVF cycle.^13^ Therefore, given the lack of evidence for the effectiveness of ES in women undergoing their first cycle of IVF/ICSI, it is essential that a large well-controlled multicentre trial is conducted to fully investigate the effectiveness and safety of this technique.

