##### Exclusion criteria

Previous trauma/surgery to the endometrium (eg, resection of submucous fibroid, intrauterine adhesions).Body mass index (BMI) of 35 kg/m^2^ or greater.Known grade 4 (severe) endometriosis.Currently participating in any other fertility study involving medical/surgical intervention.Expected to receive protocols other than antagonist or long (eg, ultralong protocol).An ES (or similar procedure, eg, endometrial biopsy for the collection of natural killer cells) is planned.Previously randomised into this trial.

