##### Study procedures

Following randomisation women in the intervention arm will have the ES procedure performed in the mid-luteal phase of the preceding cycle prior to their planned IVF/ICSI cycle in the outpatient setting of the fertility unit. The choice of screening for infection prior to the procedure or the administration of antibiotics will be left to individual units according to their local established protocols and procedures. Women can be randomised any time up until they start their IVF cycle, although it may be necessary for the participant to delay her IVF if randomised to the intervention arm. This decision to delay should be made and agreed by both the patient and her fertility team before randomisation is undertaken. The contraceptive pill/oral contraceptives can be used following randomisation for the purposes of cycle programming, but women must be having ovulatory periods at the point of entry into the trial. Women randomised to TAU will continue with their IVF/ICSI as planned and will not receive the ES procedure.

Following delivery of the ES, participants will undergo IVF/ICSI in line with local procedures. Following successful embryo transfer (in both groups), a pregnancy test will be performed and adverse events (AEs) will be collected. In cases where women do not undergo embryo transfer, every effort will be made by the research team to collect any AE information from either the patient or the medical notes. If a pregnancy is confirmed, the woman is discharged to normal antenatal care as per standard practice. It is the intention to obtain the pregnancy status of all women once randomised including the outcome of all spontaneous pregnancies, the first frozen embryo transfer if no fresh transfer has been undertaken as well as those that delay treatment following the ES. Women will not be followed up if they withdraw their consent from the trial. Data will also be collected regarding participants who have received an ES outside the trial.

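### The per-protocol control set does not require that no endometrial scratch was received, and the cycle-timing condition removes delayed women from the scratch arm only

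*Protocol article*

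**What the plan says.** All references are to the protocol article.

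- **Primary population.** Statistical analysis: "Primary analysis will be performed on the intention-to-treat population (all participants randomised into the trial".
- **Role of the PP analysis.** Same section: "For sensitivity analyses, PP analyses will also be undertaken".
- **PP rule, ES arm.** Same section: "receiving the ES procedure as documented in the study protocol and undergoing IVF/ICSI in the subsequent menstrual cycle, including embryo transfer".
- **PP rule, control arm.** Same section: "For the control group, the PP population will receive IVF/ICSI including embryo transfer".
- **What controls are meant to receive.** Study procedures: "Women randomised to TAU will continue with their IVF/ICSI as planned and will not receive the ES procedure".
- **ES obtained elsewhere.** Study procedures: "Data will also be collected regarding participants who have received an ES outside the trial".
- **Availability of ES.** Background says that ES "is currently being provided in some fertility units where women are having IVF/intracytoplasmic sperm injection (ICSI) for the first time".
- **Entry restriction.** Among the exclusion criteria: "An ES (or similar procedure, eg, endometrial biopsy for the collection of natural killer cells) is planned".

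Study procedures also foresees that some women will put off treatment after the ES, and it seeks their pregnancy status.

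**The concern.** A PP set is meant to compare women who had the care assigned to them. For controls, that care is IVF/ICSI without ES. The stated control rule checks the first part and not the second, so a control who crossed over to ES stays in the set as an adherent control. The article itself shows that this can happen: ES is on offer in some units for first cycles, participants are not blinded, and ES outside the trial is recorded. The exclusion criterion covers only an ES already planned at entry, not one arranged after randomisation.

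The second difference is timing. An ES woman whose IVF/ICSI slips past the next cycle leaves the PP set; a control whose IVF/ICSI slips by the same amount stays. If delay is related to prognosis, the two sets are no longer comparable.

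At stake is how the comparison of PP with ITT is read. A PP estimate close to ITT would normally be taken as reassurance about non-adherence. Here it could also reflect dilution from treated controls, or two biases that offset each other.

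**Working it through.** **The plan's own figure.** Inputs from the Sampling section: LBR 30% against 40%, two-sided 5% level, 90% power, 5% drop-out.

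- Uncorrected: n = [1.960 × √(2 × 0.35 × 0.65) + 1.282 × √(0.30 × 0.70 + 0.40 × 0.60)]² / 0.10² ≈ 476.0, rounded up to 477 per group.
- With continuity correction: n/4 × [1 + √(1 + 4/(n × 0.10))]² = 496 per group, as stated, so 992 in total.
- Drop-out: 992/0.95 = 1044.2, stated as 1044.

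The sample size reproduces, and nothing in this point changes it.

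**Is the asymmetry in the text?** The two rules side by side:

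| Condition | ES arm | Control arm |
|---|---|---|
| Assigned ES status met | required (ES as documented) | not required |
| IVF/ICSI in the next cycle | required | not required |
| Embryo transfer | required | required |

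Nothing elsewhere in the article adds the two missing control conditions to the PP set. Embryo transfer is required in both arms, so it is not an asymmetry.

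**Dilution by treated controls.** Let c be the share of PP controls who had an ES; the article gives no value, so c is assumed. Assume also that such women get the full planned effect.

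- Control PP rate = 0.30(1 − c) + 0.40c.
- PP difference = 0.40 − that rate = 0.10(1 − c).

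| c | PP difference (points) |
|---|---|
| 2% | 9.8 |
| 5% | 9.5 |
| 10% | 9.0 |
| 20% | 8.0 |

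On these assumptions, requiring no ES of PP controls restores 10.0 points.

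**One-sided removal of delayed women.** Suppose there is no true effect, overall LBR is 30% in both arms, a share d is delayed in both arms, and delayed women have LBR p. Both d and p are assumed. Delayed women leave the ES arm only.

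- ES PP rate = (0.30 − d × p)/(1 − d); control PP rate = 0.30.
- Spurious difference = d(0.30 − p)/(1 − d).

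| d | p = 20% | p = 40% |
|---|---|---|
| 10% | 0.01/0.90 = +1.1 points | −1.1 points |
| 20% | 0.02/0.80 = +2.5 points | −2.5 points |

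If the same timing rule operated in both arms, the spurious difference in this model would be 0.

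**Both together.** With a true effect of 10 points, d = 10% and c = 10%, the PP difference is (0.30 − 0.10p)/0.90 + 0.10 − 0.31. That is 10.1 points when p = 20% and 7.9 points when p = 40%. In the first case the two errors nearly cancel and the PP result looks correct by accident.

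**Scale.** At 496 per group and 30% LBR, the 95% half-width for a difference is 1.96 × √(2 × 0.30 × 0.70/496) = 5.7 points, and a smaller PP set would give a wider one. The shifts above are smaller than sampling error, but they are systematic.

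**The case against.** The strongest reply is that the set is called per protocol, and the protocol says controls do not have ES; a control who has one is a deviator, and the full protocol or analysis plan may say so. This has some force, because the article condenses a longer document. But the article does not leave the definition open. It states a membership rule for each arm, spells out ES status for one arm and omits it for the other. A programmer applying the stated rule would keep the treated control.

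The second reply stands in large part. The interval from ES to IVF/ICSI is part of the intervention and exists only in the ES arm, so the same condition cannot simply be copied to controls, who have no ES from which to count. Nor does every delay breach the condition: a delay agreed before randomisation to fit the ES in need not. The remedy therefore has to be a second analysis or a differently anchored window.

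Third, excluding women for events after randomisation is a general weakness of PP analysis, which is why it is only a sensitivity analysis here. That is fair.

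A reader might go further and infer that delayed women have a poorer prognosis, so that the PP analysis leans towards benefit. The article gives neither a delay rate nor a prognosis for these women, and the sign reverses if they do better than average.

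**Conclusion.** The point holds for the PP sensitivity analysis. The control rule as stated keeps women who had an ES, against the article's own description of control care. The resulting dilution is modest: 0.5 to 1 point out of 10 at an assumed 5-10% contamination with full effect in those women. The one-sided timing condition adds a possible shift of about 1 to 2.5 points, of unknown sign, if 10-20% are delayed and their LBR differs from average by 10 points. None of these rates is in the article.

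Two stronger readings are not supported. One is that the trial's main result is compromised: ITT includes every randomised woman whatever the PP rule says. ES among controls would dilute ITT too, but that follows from what happens in the trial, not from this definition. The other is that the PP result would be uninterpretable: at plausible rates it is ambiguous by a point or two. This is a wording repair worth making before unblinding.

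**What to change.** 1. Add to the control PP definition that the woman received no ES, within or outside the trial, between randomisation and embryo transfer. The trial already plans to collect the data for this.
2. Report the PP analysis a second time without the next-cycle condition in the ES arm, or with a comparable window in both arms, counted from randomisation or from the planned start of IVF/ICSI. State in the report that the ES-to-IVF interval has no counterpart among controls.
3. Optionally, add a complier-average causal effect analysis that keeps all randomised women. Its exclusion restriction must be stated. Coding a mistimed ES as untreated assumes that it has no effect, while Background cites a trial of ES at oocyte retrieval with an odds ratio of 0.30 for clinical pregnancy. Taking any ES as the treatment avoids that particular assumption.

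Cost: wording in the PP definition, a slightly smaller PP control set and one extra sensitivity run. Removing treated controls is itself a post-randomisation exclusion, so the number removed in each arm, with reasons, should be reported beside the result.

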**Trial registration number:**

ISRCTN23800982; Pre-results.

Strengths and limitations of this studyThis is the largest multicentre, pragmatic randomised controlled trial to date which aims to assess the effectiveness and cost-effectiveness of performing the endometrial scratch (ES) procedure in women having in vitro fertilisation (IVF)/intracytoplasmic sperm injection (ICSI) for the first time.It aims to determine whether performing an ES is an acceptable and well-tolerated procedure.Due to the nature of the intervention, it is not possible to blind study participants or clinicians.Potential difficulty with recruitment if patients are not in equipoise about effectiveness of the ES procedure in first-time IVF/ICSI cycles.

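### At least three of the six planned subgroup variables (day of transfer, single or double, fresh or frozen) arise after randomisation, so scratch effects within them are not randomised comparisons

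*Protocol article*

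**What the plan says.** The Statistical analysis section of the protocol article says that subgroup analyses will "explore the effect of important variables related to the participant and their treatment on the primary and secondary outcomes". Its five list items hold six variables:

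- "Day of embryo transfer (day 2, 3, 4, 5 or 6")
- "Fertilisation method (IVF, IVF or ICSI, ICSI (spilt"))
- "Type of protocol (long or antagonistic")
- single or double transfer
- fresh or frozen embryo (in the same list item as single or double)
- earlier consecutive miscarriages, 0–2 against 3 or more

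On timing, the Study procedures section says: "Women can be randomised any time up until they start their IVF cycle". It also says: "Following randomisation women in the intervention arm will have the ES procedure performed in the mid-luteal phase of the preceding cycle". The Secondary outcomes section counts among the trial's outcomes "the number of embryos replaced and day of embryo replacement". The Sampling section makes all women randomised to each group the denominator of the live birth rate (LBR).

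**The concern.** A subgroup analysis keeps the benefit of randomisation only if group membership was settled before allocation. When membership depends on what happened during the IVF cycle, the women in a given category can differ between arms in prognosis, even if each arm as a whole is balanced. An apparent benefit or harm of ES in, say, the double-transfer group can then come from who ended up there.

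Two of these variables are also secondary outcomes, and the subgroups are to be applied to the secondary outcomes. Read literally, the plan would estimate the effect of ES on day of transfer within groups defined by day of transfer.

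The list is fixed in the article itself, so this is not a detail left to an analysis plan that is not shown.

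**Working it through.** **Step 1. When is each variable known?** Randomisation precedes the IVF cycle, and ES is given in the cycle before it. Egg collection, fertilisation and transfer follow.

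| Variable | Fixed at randomisation? | Listed secondary outcome? |
|---|---|---|
| Day of transfer | No | Yes |
| Single or double transfer | No | Yes (number replaced) |
| Fresh or frozen embryo | No | No |
| Fertilisation method | Unclear: planned or actual not stated | No |
| Stimulation protocol | Yes (stratification factor) | No |
| Miscarriage history | Yes | No |

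A planned-value reading is not open for single/double or fresh/frozen. The Inclusion criteria require that single transfer and fresh embryos are expected for every woman, so planned values would have one level each. The count is therefore 3 of 6 for certain, and 4 of 6 if fertilisation method means the method used.

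**Step 2. Who has no subgroup?** Study procedures foresees women without an embryo transfer. They have no value for day, number or fresh/frozen, so those three analyses cannot cover all women randomised. The frozen group is also selected: the first frozen transfer is followed only where no fresh transfer took place.

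**Step 3. The plan's own figure.** The sample size is not touched by this point. For 30% against 40%, 5% two-sided and 90% power, the pooled-variance formula gives 477 per group, and 496 with continuity correction, which matches the article. 992/0.95 = 1044.2, against 1044 stated, or 522 per arm.

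**Step 4. Can a false effect arise?** ES has no effect on any woman's outcome below. The 30% LBR is from the Sampling section; every other rate is assumed.

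(a) *Unequal loss before transfer.* LBR is 30% in both arms, and 6% of women under treatment as usual (TAU) have no transfer. All births are taken to follow a transfer, so the extra ES women without one are women who would have failed anyway.
- ES no-transfer 8%: 0.30/0.92 = 32.6% against 0.30/0.94 = 31.9%, a false +0.7 points.
- ES no-transfer 10%: 0.30/0.90 = 33.3% against 31.9%, a false +1.4 points.

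(b) *Unequal single transfer in poorer-prognosis women.* Half the women have LBR 40% and single transfer in 80% (both arms). Half have LBR 20% and single transfer in 40% under TAU. Overall LBR is 30% in both arms.
- Under TAU, single: (0.16 + 0.04)/0.60 = 33.3%; double: (0.04 + 0.06)/0.40 = 25.0%.
- ES with 50% single in the poorer half: single (0.16 + 0.05)/0.65 = 32.3%, a false −1.0; double (0.04 + 0.05)/0.35 = 25.7%, a false +0.7.
- ES with 60%: single (0.16 + 0.06)/0.70 = 31.4%, a false −1.9; double (0.04 + 0.04)/0.30 = 26.7%, a false +1.7.

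(c) *Good-prognosis women moved to double transfer.* Under TAU, 80% have single transfer (LBR 36%) and 20% double (LBR 20%). Under ES a share s of all women, with LBR 36%, moves to double. Double-transfer LBR under ES is (0.20 × 0.20 + 0.36s)/(0.20 + s):
- s = 2%: 21.5%, a false +1.5 points
- s = 5%: 23.2%, a false +3.2 points
- s = 10%: 25.3%, a false +5.3 points

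The single-transfer groups do not differ. Overall LBR is 0.80 × 0.36 + 0.20 × 0.20 = 32.8% in both arms.

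**Step 5. Set against precision.** In (b) at 60%, single-transfer numbers are 0.60 × 522 = 313 and 0.70 × 522 = 365. The standard error is √(0.333 × 0.667/313 + 0.314 × 0.686/365) = 3.6 points, so the bias of 1.9 is about half a standard error. In (c) at s = 10%, double-transfer numbers are 104 and 157. The standard error is √(0.20 × 0.80/104 + 0.253 × 0.747/157) = 5.2 points, so the bias is about one standard error.

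**The case against.** The strongest reply is that the article promises little. It says only that the analyses will explore, and it names no interaction test, within-subgroup p value or claim. Taken literally, the wording could even mean the prognostic effect of the variables rather than the ES effect within them. Models and caveats commonly go into the analysis plan. This limits how much harm the list can do. But subgroup analysis in a two-arm trial ordinarily means the treatment effect by subgroup, and an exploratory label does not make the arms comparable or place the women without a transfer.

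Other parts of the reply stand in full:

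- A reader might infer that most of the subgroups are post-randomisation. The text establishes half, because fertilisation method may be the planned one. The split category and the reference to treatment point towards the actual method but do not settle it.
- A reader might infer that unblinded clinicians will steer women into categories. The strengths and limitations list says "Due to the nature of the intervention, it is not possible to blind study participants or clinicians", but no section says who chooses day or number, or that the choice depends on arm. Open allocation makes an imbalance possible; it does not show one.
- A reader might infer that women without a transfer will be dropped unreported. The article does not say how they are handled in these subgroups. For the primary outcome, women who do not conceive or have no IVF count as non-live births, and following first frozen transfers makes the no-transfer group smaller.
- The illustrations are assumed. (a) takes the extra women without a transfer as certain failures, and any transfer is not itself a listed subgroup. (b) calls half the women poor prognosis although the trial enrols expected good responders, and shifts single transfer by 10 to 20 points in that half.

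**Conclusion.** The point holds for at least three of six subgroup variables, two of which are also secondary outcomes. ES-against-TAU contrasts within them are not randomised comparisons and leave the all-randomised denominator. Under the assumed rates the false differences run from roughly 1 to 5 points in either direction. They are small beside the 10-point target and no more than about one standard error in the two cases checked. They show that the bias can occur, not how large it will be.

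Two stronger readings are not supported. The primary intention-to-treat result is not affected. Nor do the documents say that the case for ES with single embryo transfer, made in the Background and Discussion, will rest on the single-transfer subgroup. Every entrant is expected to have a single transfer, so the intention-to-treat comparison already addresses a population intended for it. The change is worth making because it is cheap and the list is already in print.

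**What to change.** - Restrict treatment-by-subgroup interaction analyses to variables fixed at randomisation: the stimulation-protocol stratum as randomised, miscarriage history, and planned fertilisation method if it was recorded before allocation. State which fertilisation method is meant. Age under 35 against 35–37, the bands used in the Sampling section, is an optional addition.
- Do not use planned number of embryos as a substitute, since the Inclusion criteria give it one level.
- Report actual day of transfer, number of embryos and fresh or frozen by arm in descriptive tables, labelled as non-randomised. Include a row for women with no transfer so that each table adds up to all women randomised. Attach no treatment-effect test or claim.

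The cost is a change of wording in the protocol and analysis plan, with no effect on sample size or the primary analysis. The sponsor gives up formal ES effects within transfer-defined groups.
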